## Abstract

**Background:**

The immunization uptake rates in Pakistan are much lower than desired. Major reasons include lack of awareness, parental forgetfulness regarding schedules, and misinformation regarding vaccines. In light of the COVID-19 pandemic and distancing measures, routine childhood immunization (RCI) coverage has been adversely affected, as caregivers avoid tertiary care hospitals or primary health centers. Innovative and cost-effective measures must be taken to understand and deal with the issue of low immunization rates. However, only a few smartphone-based interventions have been carried out in low- and middle-income countries (LMICs) to improve RCI.

**Objective:**

The primary objectives of this study are to evaluate whether a personalized mobile app can improve children’s on-time visits at 10 and 14 weeks of age for RCI as compared with standard care and to determine whether an artificial intelligence model can be incorporated into the app. Secondary objectives are to determine the perceptions and attitudes of caregivers regarding childhood vaccinations and to understand the factors that might influence the effect of a mobile phone–based app on vaccination improvement.

**Methods:**

A mixed methods randomized controlled trial was designed with intervention and control arms. The study will be conducted at the Aga Khan University Hospital vaccination center. Caregivers of newborns or infants visiting the center for their children’s 6-week vaccination will be recruited. The intervention arm will have access to a smartphone app with text, voice, video, and pictorial messages regarding RCI. This app will be developed based on the findings of the pretrial qualitative component of the study, in addition to *no-show* study findings, which will explore caregivers’ perceptions about RCI and a mobile phone–based app in improving RCI coverage.

**Results:**

Pretrial qualitative in-depth interviews were conducted in February 2020. Enrollment of study participants for the randomized controlled trial is in process. Study exit interviews will be conducted at the 14-week immunization visits, provided the caregivers visit the immunization facility at that time, or over the phone when the children are 18 weeks of age.

**Conclusions:**

This study will generate useful insights into the feasibility, acceptability, and usability of an Android-based smartphone app for improving RCI in Pakistan and in LMICs.

**Trial Registration:**

ClinicalTrials.gov NCT04449107; https://clinicaltrials.gov/ct2/show/NCT04449107

**International Registered Report Identifier (IRRID):**

DERR1-10.2196/22996

## Introduction

### Background

Pakistan has an under-5 mortality rate of 69.3 per 1000 live births [1], and is one of the five countries that contributed to half of the under-5 deaths in 2018, with 70% of the deaths being attributed to infectious diseases [2,3]. Pakistan ranks third among countries with the lowest immunization rates for diphtheria-tetanus-pertussis (DTP)–containing vaccine; 40% of children not vaccinated with a 3-dose series of DTP vaccine in 2015 belonged to Pakistan [4]. The low vaccine coverage has led to a number of challenges, including uninterrupted polio transmission and measles outbreaks [5]. In 2013 alone, a measles outbreak resulted in 14,000 cases with 306 deaths [6].

According to the nationwide 2017-2018 Pakistan Demographic and Health Survey (PDHS), 66% of children between the ages of 12 and 23 months had all received the basic vaccines, but only half of the children had age-appropriate vaccines [7]. The yearly PDHS surveys since 1990 have consistently shown that the coverage for age-specific vaccines falls as children grow older, with the highest coverage being seen with the birth vaccine, bacillus Calmette Guérin (BCG) (85%), and the lowest coverage being seen for the 9-month measles-1 vaccine (61%) [8]. In another study, the rate of timely BCG vaccination was 89.3%, with the measles-2 vaccine, given at 15 months of age, having a drop of 2.3% [9]. Low rates of age-appropriate vaccination, even with relatively higher rates of late immunizations, can be extremely detrimental for children as they prolong the duration for which they are vulnerable to illnesses [10].

The barriers preventing widespread immunization are multifaceted, including lack of financing, lack of good governance, supply chain interruption, and lack of awareness in the local population [8]. A case study on the Expanded Programme on Immunization (EPI) in Pakistan considered community misperceptions and misinformation to be one of the most important issues; the program recommended addressing misinformation while taking the local context into account, as the perceptions can vary from region to region and blanket communication may not resonate with all of the communities [11]. Losing vaccination cards is another major reason for low uptake, as many families rely on vaccination cards to know when it is time for the next vaccine. In one study performed on 10,000 caregivers, 76.9% did not have vaccination cards or were missing some data regarding their vaccination status [10]. With a further decrease in immunization rates due to the COVID-19 pandemic, vaccination coverage has plummeted to an all-time low due to disruption in vaccination services and demand, causing new outbreaks of previously controlled diseases, such as new polio strains, measles, and rubella [12]. Therefore, innovative and cost-effective measures need to be taken to understand and address the causes of low immunization rates.

Mobile phones provide an innovative and cost-effective public health intervention and the number of cellular phone subscribers in Pakistan has been steadily growing, with 166 million subscribers as of May 2020 and a tele-density of 78% [13]. Mobile apps and social media have been shown to be effective in various public health programs in developed countries [14-16]. However, the data from low- and middle-income countries (LMICs) are limited on the use of mobile phone–based interventions for improving routine childhood immunization (RCI) coverage; however, a few studies have shown significant promise, even when no additional financial incentives were provided to participants [17]. Most of these studies have used one-way reminder SMS text messages as the study intervention and a few used different forms of messages, such as two-way messages, educational messages, or personalized messages addressing the barrier specific to the recipient [18-23]. There is a need to invest our focus into research that explores the use of mobile phone technology and the design of robust interventions to better understand the utility of these gadgets to bring about a change in the traditional health system.

### Study Objectives

#### Primary Objectives

Our first objective is to evaluate whether a personalized mobile app can improve on-time visits at 10 and 14 weeks of age for RCIs as compared with standard care. Our second objective is to evaluate whether an artificial intelligence (AI)–based model can be incorporated into the app to improve RCI coverage and behavior change.

#### Secondary Objectives

Our secondary objectives are to learn about the perceptions and attitudes of caregivers regarding childhood vaccinations and to find out about factors that might influence the use of mobile phone–based apps for improvement in vaccination coverage.

## Methods

### Target Population

Our target population is caregivers of newborns or infants visiting the Aga Khan University Hospital (AKUH) vaccination center for their children’s 6-week vaccination and whose children are due for their RCIs at ages 10 and 14 weeks, according to Pakistan’s EPI schedule.

### Study Goal

The study goal is to conduct a mixed methods study to assess the acceptability and usability of a personalized, smartphone-based, behavioral intervention to improve vaccine uptake at 10 and 14 weeks of age, according to Pakistan’s EPI and the recommended schedule.

### Study Hypothesis

An Android smartphone–based personalized app will improve vaccination uptake among children at 10 and 14 weeks of age compared to standard care.

### Outcomes

#### Primary Outcomes

We aim to see the following primary outcomes: (1) a 10% increase in RCI through a personalized smartphone–based app at 10 and 14 weeks of age, according to the EPI schedule, versus standard care and (2) a 10% increase in RCI within 1 week of the original timeline at 10 and 14 weeks versus standard care.

#### Secondary Outcomes

We aim to achieve the following secondary outcomes: (1) to understand the perceptions and barriers of caregivers regarding immunization, (2) to understand caregivers’ perceptions, acceptability, and usability of a personalized mobile phone–based app for vaccination improvement, and (3) to achieve 85% accuracy in correctly predicting the likelihood of children defaulting from subsequent RCI visits.

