### Development of the AI-Enabled App

AI is being applied in this study in two different manners. First, AI is being applied to the baseline data and RCT results from a previous study, which is based on an automated SMS text message and voice call intervention [25]. Paigham-e-Sehat is a recently completed study that includes data from 3300 children, in which RCI-related messages were sent to caregivers via SMS text messages or automated calls to improve their children’s vaccine coverage at 6, 10, and 14 weeks of age. An AI model, using decision tree classification, random forest, naïve Bayes, and k-nearest neighbor algorithms, generated through that study is being used to train the system for predicting the likelihood of a family defaulting from subsequent RCI visits. This system will be tested during this study by validating the system’s prediction ability against the actual outcome of this study. Further, the important predictors and barriers identified in the previous study will be used for extending the work on data obtained from this study [25]**.** After the availability of the study results, factors related to the effect of users’ app behavior on the vaccination outcomes, including their preferred modes, timing, and interactivity with the app, will be analyzed through pattern recognition using a mixture of hidden Markov models. These findings will then be used to train the next version of the app to automatically adjust to individual user behaviors that have been found to be effective in improving RCI coverage (eg, the pattern recognition may identify a cluster of participants that have a better chance of getting their children immunized if they interact with app notifications during the weekend, when they are more likely to plan the next week).

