#### Sample Population and Size

Target enrollment is 328 infants, 164 in each arm; assumptions used for calculating sample size are an increase in RCI coverage rate from 40% to 60%, power of 0.80, α error rate of .05, and allowing for 10% dropout [27].

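### The 85% accuracy target for the default-prediction model is scored against an outcome the app is meant to change, with no stated handling of arm and no base-rate benchmark

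*Protocol article*

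**What the plan says.** The second primary objective in the protocol article (Study Objectives) is to see whether an AI model can be built into the app. The only numerical criterion for that model is the third item under Secondary Outcomes: "to achieve 85% accuracy in correctly predicting the likelihood of children defaulting from subsequent RCI visits".

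Development of the AI-Enabled App gives the training source and the yardstick. The model comes from an earlier trial of SMS and automated-call messages with 3300 children. What was "generated through that study is being used to train the system for predicting the likelihood of a family defaulting from subsequent RCI visits" is then checked here: "This system will be tested during this study by validating the system’s prediction ability against the actual outcome of this study".

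The Study Hypothesis gives the expected effect on that outcome: "An Android smartphone–based personalized app will improve vaccination uptake among children at 10 and 14 weeks of age compared to standard care". Sample Population and Size plans for coverage rising from 40% to 60%, with 164 infants per arm. Primary Outcomes gives a different size, "a 10% increase in RCI through a personalized smartphone–based app at 10 and 14 weeks of age".

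The article does not say whether validation is done by arm or pooled, whether arm or message exposure is a model input, or what accuracy an uninformative rule would reach.

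**The concern.** Metric, threshold and reference standard are all stated, and together they make a fragile criterion.

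First, a model that correctly identifies a child who would default under usual care is marked wrong when the app brings that child in. If the arms are pooled, a more effective app will tend to make such a model look worse.

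Second, the proportion correctly classified depends on how common default is. A threshold of 85% means one thing when 60% default and another when 15% do.

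At stake is the conclusion on the AI component: meeting or missing 85% could reflect the app's effect or the attendance rate as well as the model's ability to find defaulters. The comparison of vaccination between arms is not affected.

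**Working it through.** The 85% is a target without a derivation, so there is no figure to reproduce.

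**Inputs from the article.** Coverage 40% in controls and 60% with the app, so the control default rate is D = 0.60 (Sample Population and Size). The alternative effect is a 10% increase, taken here as 10 points, 40% to 50% (Primary Outcomes; the reading as points is an assumption). Allocation is 1:1, 328 infants, 164 per arm, 10% dropout.

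**Assumptions, not in the article.** Accuracy means the proportion correctly classified. The model predicts default without the app. The arms are pooled. Sensitivity (se) and specificity (sp) are equal, at a common value x from 0.85 to 1.00. The app turns a share r of would-be defaulters into attenders and has no effect in the other direction. In the base case r does not depend on the model's flag.

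**Formulas.**
- Control accuracy = se·D + sp·(1−D)
- App-arm accuracy = se·D·(1−r) + (1−se)·D·r + sp·(1−D)
- Pooled accuracy = mean of the two (1:1)

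**40% to 60%, x = 0.85.** r = 0.20/0.60 = 1/3.
- Control: 0.85×0.60 + 0.85×0.40 = 0.85
- App: 0.85×0.40 + 0.15×0.20 + 0.85×0.40 = 0.34 + 0.03 + 0.34 = 0.71
- Pooled: (0.85 + 0.71)/2 = 0.78

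**40% to 50%, x = 0.85.** r = 0.10/0.60 = 1/6.
- App: 0.85×0.50 + 0.15×0.10 + 0.34 = 0.78
- Pooled: (0.85 + 0.78)/2 = 0.815

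| x (se = sp) | Control | App, 40→60 | Pooled, 40→60 | App, 40→50 | Pooled, 40→50 |
|---|---|---|---|---|---|
| 0.85 | 85% | 71% | 78% | 78% | 81.5% |
| 0.90 | 90% | 74% | 82% | 82% | 86% |
| 0.95 | 95% | 77% | 86% | 86% | 90.5% |
| 1.00 | 100% | 80% | 90% | 90% | 95% |

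Pooled accuracy is 0.8x + 0.1 for the larger effect, so 85% needs x = 0.75/0.8 = 0.9375. For the smaller effect it is 0.9x + 0.05, so 85% needs x = 0.80/0.9, about 0.89.

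**If conversion depends on the flag (x = 0.85).** Of the 60% who would default, 0.51 of all children are flagged and 0.09 are missed; 0.34 are correctly predicted attenders.
- 40→60, only flagged defaulters converted: app (0.51 − 0.20) + 0.34 = 0.65; pooled 0.75.
- 40→60, missed defaulters converted first: app (0.51 − 0.11) + 0.09 + 0.34 = 0.83; pooled 0.84.
- 40→50, only flagged: app 0.41 + 0.34 = 0.75; pooled 0.80.
- 40→50, missed first: app 0.50 + 0.09 + 0.34 = 0.93; pooled 0.89.

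**Base rate.** The rule that nobody defaults has accuracy equal to coverage.
- Planning rates: 50% pooled. The best constant rule within one arm reaches 60%.
- The national 66% in the Background section: 66%.
- Assumed coverage of 80% and 90%: 85% pooled, which meets the target with sensitivity 0 for default. At those rates a model with x = 0.85 has app-arm accuracy 0.85×0.10 + 0.15×0.10 + 0.85×0.80 = 0.78, hence 81.5% pooled, and misses it.

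**Precision at 85% accuracy**, half-width 1.96·√(0.85×0.15/n): 3.9 points at n = 328, 5.5 at n = 164, and 5.8 at n = 148 (164 × 0.9 = 147.6).

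**The case against.** The strongest reply is that this is a condensed article. It does not say that the arms will be pooled or that accuracy will be the only measure; analysis by arm, cut-offs and calibration are commonly left to a fuller document. That stands as far as it goes: pooling is a possibility left open, and the figures above are conditional on it. It does not remove the point, because the article itself fixes the metric, the threshold and the reference outcome.

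The second reply is that the model was trained on a messaging trial. Its labels may already reflect messages, and exposure may be an input, so attendance in the app arm is not automatically a prediction error. This also stands, and it bears on the remedy: how well controls match the training setting depends on how exposure was modelled.

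Third, the loss shrinks under the smaller effect. At 10 points a model with x = 0.90 passes, and one with x = 0.85 may pass if the app mainly reaches defaulters whom the model missed.

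Two stronger readings are tempting. A reader might infer that a useless model would pass in this trial. The planning rates do not support that: a constant rule scores 50% pooled and at most 60% within an arm. Recruitment at the 6-week visit and the exclusion of families who do not plan to return make higher coverage plausible, but the article gives no figure near 85%. A reader might also infer that the target measures nothing about prediction. With a no-information rate of 50% to 60%, an accuracy of 85% is informative; the measure is imperfect, not empty.

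**Conclusion.** The point holds in conditional form. The sole stated AI criterion ties a fixed accuracy threshold to an outcome that the app is intended to alter, without stating how arm is handled or what the base rate would give.

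If the model predicts default without the app and the arms are pooled, a model with assumed sensitivity and specificity of 0.85 misses 85% across the whole range examined at the 40% to 60% effect. At a 10-point effect it misses in the base case but not at the upper end of the range. A stronger model, with x of about 0.94 or about 0.89 respectively, would still reach the target.

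The base-rate weakness is one of principle at the planning rates and becomes practical only if coverage approaches 85%. The matter should be corrected because the AI conclusion would otherwise be hard to interpret, but it does not touch the main vaccination comparison.

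**What to change.** - Make the control arm the primary validation set and report the app arm separately. State whether message exposure in the earlier SMS and call trial was a model input and, if so, how it is set for controls.
- Report AUC, and sensitivity and specificity for default at a cut-off fixed before trial outcomes are examined, each with a 95% CI. A rule that predicts attendance for every child then shows AUC 0.50 and sensitivity 0 at any coverage.
- If the 85% accuracy target is kept, say that it means the proportion correctly classified, and also require it to exceed the no-information rate, the larger of the default and non-default proportions in the validation set.

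The cost is wording and some added analysis; data collection does not change. The price is precision: validation in about 148 to 164 children gives a 95% CI half-width of about 5.5 to 5.8 points, against about 3.9 with all 328.

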### Study Site

This study will be conducted at the AKUH in Karachi, Pakistan. The caregivers visiting the vaccination center at the AKUH Community Health Center (CHC) will be enrolled in the study.

### Study Design

A mixed methods study will be conducted in which a smartphone app will be developed based on the findings of the qualitative component of the study, in addition to *no-show* study findings [24]. The smartphone app will include text, voice, video, and pictorial messages to help the caregiver participants adhere to their children’s RCI schedules at 10 and 14 weeks of age.

### Qualitative Component: Pretrial Interviews

The qualitative component of this study involves determining caregivers’ perceptions about RCI and the role of the mobile phone–based app in improving RCI coverage. In-depth interviews will be conducted with the caregivers visiting the CHC vaccination center. We explored the caregivers’ perceptions and attitudes regarding childhood vaccination, the reasons for missed visits at the CHC vaccination center, the perceived role of staff and services provided through the CHC vaccination center, the usability and acceptability related to the use of the personalized mobile phone–based app for improvement in vaccine uptake, the potential barriers related to the app’s usage, and their expectations of the app regarding reminders for RCI coverage and timeliness. We used the purposive sampling strategy to interview 15-20 consenting parents over 15 days. This method of sampling allows for the identification of well-informed participants who can provide insights and personal experiences regarding the subject being examined. A semistructured interview guide was developed in English and Urdu and was further modified after each pilot interview to explore the concerns recognized through constant analysis of consecutive interviews. Data collection continued until data saturation was reached. Each interview took around 30-45 minutes. Information gathered through the interviews helped us in (1) understanding the types of RCI and mobile phone app barriers perceived by caregivers, (2) designing the randomized controlled trial (RCT), and (3) developing a mobile app.

### Intervention

An Android-based mobile app is being developed. The app will have features and capacity for text, voice, pictorial, and video messages. The content of the messages will be based on the previous study that utilized automated SMS text messages and calls in various local languages to improve RCI coverage [25].

The four message domains will be educational, reminder, religious, and adverse effects. In addition, pictorial and video messages freely available through open sources focusing on immunization among children in Pakistan will be utilized.

### Development of the Smartphone App

This smartphone app, as part of the Capacity Building in Technology-Driven Innovation in Healthcare (CoNTINuE) project, will be developed on an Android platform, as 95% of smartphone users in Pakistan use Android phones [26]. Functionality validation exercises will be carried out using cognitive validation and cultural probes before using the app in this research. The app will be installed on the phones of the participants in the intervention arm by the study administrators. Once the app has launched and privacy policies have been accepted, the participants will be asked to enter information into the app, including their child’s medical record number, their child’s date of birth, their preferred mode of messages such as audio or text, their language and time preferences to receive the messages, and the barriers they face to vaccinate their child; these features will help personalize the type and content of messages they will receive. The data will be stored in local secured systems and immediately anonymized using digitally available tools to ensure privacy and avoid any potential identity breach.

After entering the enrollment data, the phone will need to be connected to the internet for a few minutes to allow for necessary content to be downloaded, which will enable timely notifications in the future. At the enrollment site, free Wi-Fi will be available for the participants. However, in the event of a disruption in downloading the app or prolonged time consumption due to the size of the app, an alternate Wi-Fi connection, whose cost is covered by the project, will be provided to download the app. This feature of one-time downloading of the data allows for the app to be functional even in the case of internet unavailability. Once the content is downloaded, the first screen to be displayed will be the app logo layout followed by the main home layout. The user can then navigate to the (1) *vaccination schedule* layout, (2) *resources* layout, (3) *notification detail* layout, or (4) *about us* layout pages, as shown in Figures 1 and 2. This app will be developed to catalyze a behavioral change in its users through its many functionalities. In the *vaccination schedule* layout, a calendar indicating the child’s specific, scheduled vaccination days will be displayed. In the *resources* layout, the users will be able to access the official websites of the EPI, the AKUH CHC, and World Health Organization vaccines, among others. The *notification detail* layout will display notifications every week regarding upcoming vaccinations or educational messages. The notifications will be displayed as summaries, and additional information and content from the text or audio message will be able to be accessed upon clicking the individual notification. The notifications will be delivered in the participant’s preferred language (ie, Urdu, English, Sindhi, Roman Urdu, and Roman Sindhi), preferred mode of messaging (ie, text or audio), and preferred time for receiving the notifications (ie, morning, afternoon, or evening). Lastly, the *about us* layout will provide insight into the vision of the CoNTINuE project. These navigation panels and their labels will also be displayed in the preferred local language. Also, at the time of enrollment, a detailed walk-through process of the app will be conducted with the caregivers.

